# Pain REduction with bone metastases STereotactic radiotherapy (PREST): A phase III randomized multicentric trial

**DOI:** 10.1186/s13063-019-3676-x

**Published:** 2019-10-28

**Keywords:** Bone metastases, Pain control, Simultaneous integrated boost, Randomised controlled trial

## Abstract

**Background:**

Palliative antalgic treatments represent an issue for clinical management and a challenge for scientific research. Radiotherapy (RT) plays a central role. Techniques such as stereotactic body radiotherapy (SBRT) were largely investigated in several phase 2 studies with good symptom response, becoming widely adopted. However, evidence from randomized, direct comparison of RT and SBRT is still lacking.

**Methods/design:**

The PREST trial was designed as an interventional study without medicinal treatment. It is a phase 3, open-label, multicentric trial randomized 1:1. Inclusion criteria include painful spinal bone metastases presenting with a pain level > 4 (or > 1 if being treated with an analgesic) on the Numeric Rating Scale (NRS); expected intermediate/high prognosis (greater than 6 months) according to the Mizumoto prognostic score; low spine instability neoplastic score (SINS) sores (< 7); magnetic resonance imaging (MRI) assessment of the bulky lesion. Patients will be assigned to either standard conventional radiotherapy involving 4 Gy × 5 fractions (fx) to the whole involved vertebra or SBRT by intensity modulated radiotherapy with simultaneous integrated boost (IMRT-SIB) involving 7 Gy × 3 fx to the whole involved vertebra + 10 Gy × 3 fx on the macroscopic lesion (gross tumor volume (GTV)). In the experimental arm, the GTV will be contoured by registration with baseline MRI.

**Discussion:**

The primary endpoint is overall pain reduction, defined in terms of variation between baseline and 3-month evaluation; pain will be measured using the NRS. Secondary endpoints include pain control duration; retreatment rates (after a minimum interval of 1 month); local control assessed with RECIST criteria; symptom progression free survival; progression-free survival; overall survival; and quality of life (at 0, 30, and 90 days). Accrual of 330 lesions is planned. The experimental arm is expected to have an improvement in overall pain response rates of 15% with respect to the standard arm (60% according to Chow et al. (Int J Radiat Oncol Biol Phys. 82(5):1730–7, 2012)).

**Trial registration:**

ClinicalTrials.gov, NCT03597984. Registered on July 2018.

**Electronic supplementary material:**

The online version of this article (10.1186/s13063-019-3676-x) contains supplementary material, which is available to authorized users.

## Background

The PREST trial (NCT03597984) includes patients with spinal bone metastases from solid tumors which present with an intermediate or high level prognosis (i.e., > 6 months) according to the Mizumoto score (i.e., classes A + B) [1]. These particular cases are often debated with regard to whether they should receive conventional antalgic radiotherapy or higher radiotherapy (RT) doses in order to better control symptoms. Technological improvements (e.g., stereotactic body radiotherapy (SBRT)) [2, 3] and advanced treatment planning (e.g., intensity modulated RT (IMRT)) [4] can enhance RT treatment efficacy by dose escalation to offer more effective pain (and potentially disease) control without compromising the organ at risk (OAR) through toxicity.

The aim of this randomized, multicentre, prospective trial is to evaluate the efficacy, in terms of pain control, of an unconventional RT fractionation (delivered by SBRT) against the standard one. The trial will enroll patients with intermediate-to-high prognosis (i.e., superior to 6 months) according to the Mizumoto prognostic score [1] and structural stability (according to the Spine Instability Neoplastic Score (SINS)) over a threshold of 7 [5]. Highlights of this study include the high level of treatment customization through both accurate selection and ultra-conformed RT planning and the reduced number of sessions (i.e., three instead of the gold standard) which patients will undergo, potentially limiting discomfort.

## Methods/design

### Aims

The PREST trial aims to assess whether RT for bone metastases administered by IMRT through a simultaneous integrated boost (SIB) can control pain symptoms better than fractionated standard three-dimensional conformal radiotherapy (3D-CRT). Providing better pain control is the crucial test for any new technique introduced in the palliative antalgic setting. Multicentre recruitment will allow more precise assessment of the intervention, with the aim of demonstrating that implementing RT in this setting is both feasible and safe among the centers. Secondary aims are to assess potential benefits for disease control, including oncological outcomes. Moreover, prolonged response to antalgic RT can avoid retreatment, thus improving quality of life in these individuals, which is an important goal.

### Overview of the design

The PREST trial investigates the use of an advanced technique to administer 7 Gy × 3 fx (to the whole vertebra) plus SIB of 10 Gy × 3 fx to the macroscopic lesion (gross tumor volume (GTV)) defined by magnetic resonance imaging (MRI), compared to 4 Gy × 5 fx on the whole vertebra (standard arm) in patients with bone metastases from solid tumor and intermediate or high level prognosis > 6 months according to the Mizumoto score. Further details of the rationale for this design are provided in the “Discussion” section. Figure 1 shows a summary schema for the trial.

**Fig. 1 Fig1:**
[figure not shown]
PREST trial (NCT03597984) schema

### Participants

Participants entering the PREST trial are affected by a solid tumor with histologically confirmed diagnosis and associated bone metastases. The estimated prognosis is intermediate or high (i.e., > 6 months) according to the Mizumoto prognostic score. Eligibility criteria are summarized in Table 1.

**Table 1 Tab1:** Summary of eligibility criteria

PREST trial eligibility criteria	
Inclusion criteria	Exclusion criteria
• Patients diagnosed with spinal bone metastases from solid, uncomplicated tumor • Primary or secondary tumor histology related to the treatment lesion • Patients aged > 18 years • Obtained informed consent • ECOG 0–2 • Symptomatic patients at the treatment site (NRS ≥ 4) • Symptomatic patients at the treatment site (NRS 1–3) assuming opioid therapy ongoing for more than 3 days • Spine Instability Neoplastic Score (SINS) < 7 • Prognosis > 6 months according to Mizumoto Prognostic Score (i.e., classes A and B) • Spinal metastases verified at MRI, including the sites to be enrolled • No more than three non-contiguous spinal segments (e.g., separated by at least two metamers) involved in the study	• Unable to assign specific NRS for each CTV to be enrolled • Unable to express autonomous consent to therapies • Pregnancy • Patient in hospice or with prognosis < 6 months • Unavailability forecast for follow-up • Absence of MRI pre-treatment study • Unable to maintain the treatment position for SBRT • Previous radiotherapy at the same site or at the level of adjoining metameres (higher or lower than the one to be enrolled) • Previous radiometabolic therapy • Previous enrolment of the same patient for three irradiated lesions • Epidural compression of the spinal cord or of the cauda equina • Injuries affecting > 25% of the medullary canal and/or a distance < 5 mm from the medulla or from the cauda • Injuries with indication of surgical stabilization • Chemotherapy or target therapy within the previous 7 days and 7 days after SBRT

### Registration

The PREST trial is promoted by Fondazione Policlinico Gemelli—IRCCS in Rome (Italy). The local Ethics Committee has approved the protocol. Each interested center will submit the protocol to its ethics committee for approval before accrual. After approval, the center will receive a dedicated electronic case report form (CRF). Eligible participants who have provided consent and meet the inclusion criteria are anonymously registered on the CRF by assigning a numerical code.

### Randomization

Following the assessment for eligibility and after informed consent is signed, eligible participants are randomized by phone to the promoting centre. Participants undergo a blind randomization using minimization algorithms based on key prognostic factors, incorporating a random element. Patients are allocated in a 1:1 ratio to either gold standard radiotherapy treatment or interventional SIB radiotherapy treatment.

### Radiotherapy

CT simulation will be carried out with custom immobilization support for each patient (Aquaplast® head mask and/or vacuum mattresses). For target delineation, co-registration with MRI will be performed using the Velocity® application. The GTV is defined as the visible lesion on MRI imaging. In the experimental arm, two volumes will be defined: PTV1, including GTV plus a 2-mm isotropic margin; and PTV2, including total vertebra plus a 2-mm isotropic margin. In the standard arm, a single volume will be contoured: PTV1 (total vertebra plus a 1-cm isotropic margin).

In the experimental arm, both the spinal canal and spinal cord will be defined on MRI imaging, and their cranial and caudal margin will be the cranial margin of superior vertebra and caudal margin of inferior vertebra, respectively. The dose constraint limit for the spinal canal will be D_max_ < 15 Gy, while for the spinal cord it will be considered both D_max_ < 10 Gy [6] and D_0.035_. For cauda, dose constraints considered will be Dmax < 24 Gy and threshold dose of 21.9 Gy to less < 5 cc [6]. Moreover, in the SIB cohort, PTV coverage should be 95% of the prescribed dose at 95% of the defined volume. Major deviation for PTV2 will be < 77% of the dose prescribed at 95% of the volume, while minor deviation will be < 84% of the prescribed dose at 95% of the volume. For PTV1, major deviation will be defined as < 79% of the prescribed dose at 95% of the volume, while minor deviation will be < 84% of the prescribed dose at 95% of the volume.

Reporting of dose prescription will be done according to ICRU 83 for the experimental arm and according to ICRU 62 for the standard arm. Furthermore, as security criteria, all treatment plan validation will rely on QUANTEC and AAPM reports for organ at risk (OAR) constraints [6, 7].

### Follow-up

Patients are assessed according to International Bone Metastases Consensus Working Party [8] criteria. Pain control will be assessed at every visit according to IBMC criteria (Additional file 1). IBMC criteria are based on pain level and ongoing antalgic opioid therapies. Pain level will be defined using the 11-point NRS. NRS score subscales evaluated will be:
0: no pain (better outcome)1–3: mild pain4–6: moderate pain7–10 severe pain (worse outcome)

Opioid therapies will be quantified according to Oral Morphine Equivalent Dose (OMED). The visit schedule is 15 days, 30 days, 3 months, 6 months, and 12 months after the end of radiotherapy. At every visit, patients will undergo quality of life measurement using the QLQ-C15-PAL and QLQ– BM22 questionnaires [9]. Other outcomes that will be tested during follow-up visits are rate of retreatment for non-responding patients, pain control duration, local control, symptom progression-free survival, progression free survival, and overall survival. Long-term passive follow-up data will be obtained from routinely collected healthcare databases for at least 10 more years.

For participants that are registered but do not go on to be randomized, active participation in the trial will end at that time. However, passive follow-up will continue via routinely collected healthcare datasets where consent for this has been obtained. The trial assessment schedule for each arm is aligned with standard practice where possible to ensure they can be implemented easily. This is balanced with the need to ensure appropriate monitoring of patients on trial treatment and assessment of outcome measures. The trial follow-up schedules are available in Additional file 2.

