## Discussion

### Outcomes

One-month pain control analysis will take place 90 days after the end of RT of the last patient. Primary and secondary outcome measures are available in Table 2.

**Table 2 Tab2:** Summary of primary and secondary endpoints

Endpoint definitions and measurement	
Primary outcome measure	
Pain control (efficacy and pain; time frame 3 months) Overall pain control measured according to IBMC (complete response + partial response events)	
Secondary outcomes measures	
• Pain control duration (efficacy and pain; time frame 12 months after end of radiotherapy) Interval from the end of the RT to relapse of the symptom • Rate of retreatments (efficacy; time frame 12 months after end of radiotherapy) Interval from the end of the RT to the start of retreatment • Local control (efficacy; time frame 3, 6, and 12 months from the end of radiotherapy) Control of local disease with diagnostic exams according to RECIST 1.1 criteria • Symptom progression-free survival (SPFS) (efficacy and pain); time frame 12 months after end of radiotherapy) Interval from the end of radiotherapy and progressive disease with symptoms according to the criteria of Chow et al. in 2012 [8] • Progression-free survival (efficacy; time frame 12 months) Interval from the end of radiotherapy and new disease progression • Overall survival (efficacy; time frame 12 months) Interval between the end of radiotherapy and death • Quality of life (efficacy and quality of life; time frame first visit, 1 month, and 3 months after the end of radiotherapy) Quality of life score according to European Organization for Research and Treatment of Cancer (EORTC) QLQ-C15-PAL and QLQ– BM22 questionnaires	

Local control and overall survival will also be assessed as secondary outcomes in all participants for 10 years. The longer follow-up and large sample size associated with this analysis will enable any long-term benefits of RT with IMRT-SIB to be determined, including number of retreatments. Consideration of rates of serious toxicity (and particularly serious myelotoxicities), as well as other secondary health outcomes, alongside the efficacy results will be particularly important in these analyses in order to provide a holistic assessment of the potential risks and benefits associated with a different schedule of RT administration.

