### Statistical considerations and sample size

Primary analysis will compare the response in terms of reduction of pain symptomatology from bone metastases, comparing the conformational RT (3D-CRT) administered in conventional fractionation versus IMRT-SIB. The study involves the enrolment of 330 patients divided into two groups of 165 patients in each of the two study arms. Arm A (standard) will recieve 4 Gy × 5 fx; arm B (experimental) will receive SIB 7 Gy × 3 fx (whole vertebra) + 10 Gy × 3 fx on the GTV (defined by MRI). The expected difference between the two treatments for one-month pain control in terms of overall response rates is 15% more in the experimental arm compared to the standard arm (60%). The calculation of the sample size considered a 95% CI with a coefficient α of 0.05 and a drop-out rate of 10%.

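### The Follow-up section limits the retreatment outcome to non-responders while Table 2 and the abstract do not; followed literally, that limit can hide or reverse a treatment effect

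*Protocol article*

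**What the plan says.** Retreatment appears in three forms in the protocol article.

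- **Follow-up (Methods/design):** among the outcomes tested at visits is the "rate of retreatment for non-responding patients". It does not say at which visit a patient is classed as a non-responder.
- **Outcomes, Table 2:** the secondary endpoint is named as a rate of retreatments over 12 months but defined as "Interval from the end of the RT to the start of retreatment". There is no limit to non-responders.
- **Abstract, Discussion:** the secondary endpoints include "retreatment rates (after a minimum interval of 1 month"), again without that limit.

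The text below Table 2 also expects the longer follow-up to inform the number of retreatments, with no restriction.

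Pain control duration is defined in Table 2 as "Interval from the end of the RT to relapse of the symptom", over 12 months. No section says how a patient who never had a response is counted.

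The Aims section gives the avoidance of retreatment through prolonged response as an important goal.

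**The concern.** Response is an outcome of the treatment. The trial is designed on the expectation that it will differ between arms, so the non-responders in one arm are not the randomised counterparts of those in the other. If the experimental treatment turns some patients into responders, those patients leave the non-responder group in one arm only, and the patients who remain may be harder to treat.

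A non-responder denominator also misses the mechanism named in the Aims. Retreatment avoided through lasting response is avoided in responders, and patients who respond, relapse and are retreated would not be counted.

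For duration, a relapse presupposes an earlier response. A never-responder censored as relapse-free would be scored as having lasting control.

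**Working it through.** **Inputs from the document** (Statistical considerations and sample size): "330 patients divided into two groups of 165 patients in each of the two study arms"; response 60% in the standard arm and 15% more in the experimental arm; alpha 0.05; drop-out 10%.

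**Check that 15% means percentage points.** Power is not stated; assume 80% and a two-sided test. With unpooled variance:

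n = (1.960 + 0.842)² × (0.60×0.40 + 0.75×0.25) / 0.15² = 7.85 × 0.4275 / 0.0225 ≈ 149.2, rounded up to 150 per arm; 150 × 1.10 = 165.

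The planned size is reproduced, which supports reading the rates as 60% v 75%.

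**Size of the non-responder groups** (before drop-out): 165 × 0.40 = 66 v 165 × 0.25 = 41.25, so about 66 v 41.

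**Case 1: the effect is hidden.** Retreatment risks are assumptions; the article gives none. Let risk be a in non-responders and b in responders, the same in both arms. The non-responder comparison is then a v a, showing no difference. Per randomised patient the rates are 0.60b + 0.40a v 0.75b + 0.25a, a difference of 0.15(a − b). With a = 30%:

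| b (responders) | Non-responders only | All randomised | Difference | Relative reduction |
|---|---|---|---|---|
| 0% | 30% v 30% | 12.0% v 7.5% | 4.5 points | 37.5% |
| 10% | 30% v 30% | 18.0% v 15.0% | 3.0 points | 16.7% |
| 20% | 30% v 30% | 24.0% v 22.5% | 1.5 points | 6.25% |

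The first row requires that no responder is ever retreated, so it is the extreme of the range.

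**Case 2: the effect is reversed or invented.** Suppose 60% respond on either treatment, 15% only on the experimental treatment, 25% on neither, and nobody responds only on standard treatment. Assume retreatment of 10% in any responder, 30% in the middle group when it goes without response in the standard arm, and 50% in the never-responding group.

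- All randomised, standard: 0.60×0.10 + 0.15×0.30 + 0.25×0.50 = 23.0%.
- All randomised, experimental: 0.75×0.10 + 0.25×0.50 = 20.0%.
- Non-responders, standard: (0.15×0.30 + 0.25×0.50) / 0.40 = 42.5%.
- Non-responders, experimental: 50.0%.

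A 3-point benefit appears as a 7.5-point harm. If the middle group's risk is 10% instead of 30%, all randomised patients show 20% v 20%, while non-responders show 35% v 50%: an apparent harm where there is no effect.

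**Pain control duration.** Let r be the 12-month relapse risk among responders in both arms, ignoring death and drop-out. If never-responders are censored as relapse-free, observed relapse is 0.60r v 0.75r, whereas the share of randomised patients still in control is 0.60(1 − r) v 0.75(1 − r). At an assumed r = 40%, relapse is 24% v 30% (experimental looks worse) and patients still controlled are 36% v 45% (experimental is better).

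**The case against.** The strongest reply is that Table 2 is where the endpoints are defined. It sets no limit to non-responders, and neither does the abstract. The Follow-up sentence is a list of what is checked at visits, and its wording may name the reason for retreating rather than a denominator. This stands in part. A reader might infer that the trial has settled on a non-responder subgroup analysis, and the document does not support that; it shows a conflict between sections.

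A reader might likewise infer that duration will be analysed in responders only. That rests on the word relapse alone. The clock starts at the end of radiotherapy, and no section restricts the population. What stands is that the stated event cannot occur in a never-responder and no rule is given for such a patient.

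It is also fair to say that estimators and censoring rules usually belong in the analysis plan, which is not shown. That covers the choice of summary measure and time origin. It does not cover an endpoint whose population is stated differently in different sections of the same article.

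Finally, 40% v 25% is non-response at the assessment used for sample size. Some of these patients may respond at another of the five visits, so for never-responders it is an upper bound.

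**Conclusion.** The concern holds as a contradiction to be reconciled, with a smaller gap beside it. Read literally, the Follow-up wording makes retreatment a comparison of post-randomisation groups of about 66 v 41 patients. Under the assumed risks it can hide a benefit of 1.5 to 4.5 points, turn a 3-point benefit into an apparent 7.5-point harm, or show harm where there is none. The group sizes rest on the planned response rates; the size of any distortion rests on retreatment risks the article does not give. It would go too far to say that neither endpoint compares the randomised arms, because Table 2's retreatment definition applies to all treated patients. The primary endpoint and the sample size are unchanged.

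**What to change.** 1. In Follow-up, delete the last three words of "rate of retreatment for non-responding patients". Use one definition in the abstract, Follow-up and Table 2, settling whether it is a rate or an interval and whether the abstract's 1-month minimum applies.
2. Analyse retreatment in all randomised patients as a 12-month cumulative incidence with death as a competing event. Label any summary in non-responders as descriptive.
3. For pain control duration, state that never-responders count as duration zero in a comparison of all randomised patients. Keep duration among responders as descriptive.

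The end-of-radiotherapy origin and the summary measure for duration (for example a restricted mean) can be left to the analysis plan.

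The cost is a change of wording, slightly more analysis, and a rule for interpolating response status between the 3-, 6- and 12-month visits. No new data are needed, since pain response is already assessed at every visit. The article reports recruitment as not completed, so the definitions can be fixed before results are known.

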### Toxicity management

Participants that experience radiotherapy-related severe toxicity, defined as ≥ Grade 3 Common Terminology Criteria for Adverse Events (CTCAE v4) [10], will be signaled in the study final report. Grade 1 and 2 toxicity are considered normal in clinical practice, but they will also be reported.

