### Final considerations

Palliative antalgic oncological treatments represent a serious problem for both clinical management and scientific research. However, they involve an ever-increasing number of patients due to the increased incidence of cancer in all its phases and the potential chronicity of illness linked to new therapies. The use of palliative RT treatments potentially involves up to 40% of patients in a radiation oncology center. RT is commonly used in palliative treatment for symptomatic bone metastases [11], being an effective treatment for improving symptoms and, consequently, the quality of life of these patients.

Ideally, this treatment should be as short as possible, re-directing patients either to systemic therapies or to home care or long-term care systems (e.g., hospices). In order to deliver a clinically effective dose in a short period, hypofractionated regimens must be used. SBRT is a technique of RT allowing delivery of a high equivalent biological dose in a highly conformed manner, with a favorable toxicity profile [3], generally in a few fractions (fx). The possibility of using special techniques such as SBRT in the palliative antalgic setting for bone metastases has been investigated in several phase 2 studies, with good results in terms of symptom response [12–17]. In order to better manage the toxicity profile of such hypofractioned regimens (mainly related to risk of vertebral fracture [18]) further studies [19, 20] have suggested the possibility of using a hypofractionated regimen over the entire bone compartment and going to over-dose with a stereotactic regimen only for the macroscopically visible disease from instrumental examinations. In patients with more favorable prognosis, this regimen could improve the possible onset of acute and late complications, while increasing the RT dose to the bulky lesion.

Literature indications about preferred RT schedules are available, although there is no globally coded and unique clinically applied therapeutic standard for prescription [8, 21]. The most commonly applied conventional radiation treatment schedules include i) 8 Gy in 1 fx, ii) 20 Gy in 5 fx, iii) 30 Gy in 10 fx [22].

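### The article's only defined severe-toxicity measure is limited to radiotherapy-related events in an open-label trial, and does not match the unqualified serious-toxicity rates it plans to weigh against efficacy

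*Protocol article*

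**What the plan says.** All references are to the protocol article.

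- **Blinding.** The Abstract (Methods/design) describes a "phase 3, open-label, multicentric trial randomized 1:1". The Randomization section says "Participants undergo a blind randomization using minimization algorithms", which concerns how patients are allocated. No masked or independent assessor of adverse events is described.
- **Toxicity rule.** Toxicity management states that "Participants that experience radiotherapy-related severe toxicity, defined as ≥ Grade 3" on CTCAE v4 will be flagged in the final report. The next sentence adds that "Grade 1 and 2 toxicity are considered normal in clinical practice, but they will also be reported", with no relatedness condition.
- **Safety aim.** The Aims section refers to multicentre recruitment "with the aim of demonstrating that implementing RT in this setting is both feasible and safe among the centers".
- **Intended use of toxicity data.** The Outcomes section says that "Consideration of rates of serious toxicity (and particularly serious myelotoxicities") will be particularly important when read with the efficacy results. That sentence has no relatedness limit, and it speaks of toxicity as though it were one of the secondary outcomes.
- **Listed outcomes.** Table 2 tags every entry as efficacy, pain or quality of life. The Follow-up section lists retreatment, pain control duration, local control, symptom progression-free survival, progression-free survival and overall survival, besides pain and quality of life. Toxicity is in neither list.
- **Main named risk.** Final considerations describes the toxicity of hypofractionated regimens as "mainly related to risk of vertebral fracture".

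**The concern.** The article uses two different quantities for severe toxicity without saying which one will be compared. The one it defines depends on a causal judgement; the one it plans to weigh against efficacy does not.

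The judgement matters more here than in most radiotherapy trials. The irradiated vertebra contains the tumour, so a fracture in it can reasonably be blamed on either. If whoever decides knows the arm, and knows that fracture is associated with hypofractionated regimens, attribution may differ by arm. It could be more readily blamed on radiation in the experimental arm, or less readily by those who favour the new technique, so the direction cannot be predicted. Randomization balances background fractures on average, but it does not balance a judgement made afterwards with the arm known.

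What is at stake is the risk side of the risk-benefit assessment of the escalated regimen. The primary pain comparison is not affected.

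**Working it through.** **What can be reproduced.** The article states no toxicity rate and no safety sample size, so there is no safety figure to reproduce. The only figure used here is 165 patients per arm (Statistical considerations and sample size). It is consistent with 60% versus 75% response, two-sided α of 0.05 and 10% dropout if 80% power is assumed (none is stated): (1.960 + 0.842)² × (0.24 + 0.1875) / 0.15² = 149.1 per arm, and 149.1 / 0.9 = 165.7. The toxicity point does not depend on this.

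**Effect of a relatedness filter.** For each arm, reported rate = true rate × probability that an event is attributed to radiotherapy. The reported ratio is therefore the true ratio multiplied by the ratio of the two attribution probabilities. All true rates and attribution probabilities below are assumptions; none is in the documents. Expected events are rate × 165, and the ratio is experimental over standard.

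| True rate, standard / experimental | Attributed, standard / experimental | Related-only events, standard / experimental | Apparent ratio |
|---|---|---|---|
| 10% / 10% | 50% / 50% | 8.25 / 8.25 | 1.0 |
| 5% / 5% | 40% / 60% | 3.3 / 4.95 | 1.5 |
| 10% / 10% | 40% / 60% | 6.6 / 9.9 | 1.5 |
| 10% / 10% | 30% / 70% | 4.95 / 11.55 | 2.3 |
| 8% / 15% | 50% / 50% | 6.6 / 12.4 | 1.875 |
| 8% / 15% | 80% / 40% | 10.56 / 9.9 | 0.94 |

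Reading the table:

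- Rows 2 to 4: a difference appears where none exists.
- Row 6: a true excess disappears (8% × 0.8 = 6.4% against 15% × 0.4 = 6.0%).
- Row 5: equal under-attribution leaves the ratio unchanged (15/8 = 7.5/4 = 1.875) but halves the absolute excess, from 7 to 3.5 points.
- Row 1: with equal true rates and equal attribution there is no distortion.

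**Effect of counting every grade 3 or higher event instead.** If background disease events occur independently with probability b in both arms, the all-cause proportion is 1 − (1 − p)(1 − b), and the difference between arms is (1 − b) times the true excess. With 15% versus 8%:

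- b = 20% (assumed): 1 − 0.85 × 0.8 = 32.0% against 1 − 0.92 × 0.8 = 26.4%; excess 5.6 points.
- b = 50% (assumed): 1 − 0.85 × 0.5 = 57.5% against 1 − 0.92 × 0.5 = 54.0%; excess 3.5 points, ratio 57.5 / 54.0 = 1.06.

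An all-cause total removes the attribution judgement, but in metastatic patients it can dilute the contrast as much as the filter does. Events defined by site avoid both problems to a large extent.

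**The case against.** The strongest opposing case has four parts.

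1. **The rule is about reporting.** A reader might infer that severe events judged unrelated will not be counted at all. The text does not support this. It says which patients are flagged in the final report; it does not say that other events go unrecorded. The following sentence reports lower grades without a relatedness condition, and the Outcomes section speaks of serious toxicity without one. This stands, and it limits the point to a mismatch between a filtered definition and an unfiltered intention.
2. **The assessor is not named.** Attribution by treating investigators who know the arm is a plausible inference from the open-label design, but the article does not say who judges. Independent review is neither described nor excluded. This also stands.
3. **This is a condensed article.** Event collection, attribution procedures and safety tables commonly sit in the full protocol, case report form or analysis plan, and Table 2 calls itself a summary. The missing safety row is therefore no finding by itself. It matters only because the article's own text treats toxicity as an important outcome while both of its outcome lists omit it.
4. **The sizes are invented, and entry criteria may keep fractures rare.** All the rates are assumptions. Eligibility requires SINS below 7 and excludes lesions with an indication for surgical stabilization, so severe fracture at 10% to 15% has no support in the documents. This stands against any claim about size. It does not remove the mechanism, since the ratio distortion is 1.5 at both 5% and 10%.

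**Conclusion.** The point holds as an inconsistency with a real route to bias. The only defined severe-toxicity measure carries a relatedness filter, no masked attribution is described, and the main named toxicity can be attributed either way. The unqualified rates that the article wants to set beside efficacy are a different quantity.

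The size is unknown. Under the assumptions shown, the apparent ratio for a true ratio of 1 ranges from 1.0 (equal attribution) to 2.3 (30% against 70%), and a true 15% versus 8% can appear as 6.0% versus 6.4%. These figures show what can happen, not what will.

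A reader might go further and conclude that the trial cannot support its safety aim. The documents do not carry that. The Aims section speaks of safety across centres, not of a test between arms, and the full protocol may specify more. What can be said is that a related-only count would weaken the planned weighing of risk against benefit. The primary analysis is untouched.

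**What to change.** Reconcile Toxicity management, the Outcomes text and Table 2 so that they refer to the same quantities, reported by arm, to 12 months and regardless of attribution:

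- **Lead safety items:** vertebral fracture at the treated level, and spinal cord injury or myelopathy. The article's term for the latter is myelotoxicity, read here as cord toxicity because the Radiotherapy section sets cord limits; the definition should make this explicit.
- **Supportive total:** the proportion of patients with any CTCAE grade 3 or higher event.
- **Supplementary column:** the radiotherapy-related judgement, kept for clinical interpretation.

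CTCAE grading and visits to 12 months are already planned, so the cost is wording, one more table and somewhat more event recording. The downside is that the all-cause total includes background disease events and may dilute the contrast substantially, which is why the site-specific items should lead. The change also does not address unequal detection: Quality assurance makes the 3-month MRI recommended but not mandatory, so the report should show how many patients in each arm were imaged.
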